## Abstract

**Background:**

Chronic musculoskeletal pain is one of the main causes of years lived with disability and generates the highest cost of health care among chronic pain conditions. Internet-based treatments have been shown to be an alternative for the treatment of musculoskeletal conditions, in addition to reducing barriers such as travel, high demands on the public health system, lack of time, lack of insurance coverage for private care, and high costs for long-term treatment. The aim of this clinical trial is to develop and test the effectiveness and cost-effectiveness of, an internet-based self-management program based on pain education and exercise for people with chronic musculoskeletal pain.

**Methods:**

This is a prospectively registered, assessor-blinded, two-arm randomised controlled trial with economic evaluation comparing the Internet-based pain education and exercise intervention with a control group that will receive an online booklet. One hundred and sixty patients will be recruited from Sao Paulo, Brazil. Follow-ups will be conducted in post-treatment, 6 and 12 months after randomisation. The conduct of the study, as well as the evaluations and follow-ups will be carried out entirely remotely, through online platforms and telephone calls. The primary outcome will be pain intensity at post-treatment (8 weeks) measured using the 11-item Pain Numerical Rating Scale. Secondary outcomes will be biopsychosocial factors presents in the chronic musculoskeletal pain condition. Costs due to chronic musculoskeletal pain will be also measured, and cost-effectiveness analysis from a societal perspective will performed.

**Discussion:**

Our hypothesis is that internet-based pain education and exercise will be better than an online booklet in reducing pain and improving biopsychosocial outcomes in patients with chronic musculoskeletal pain. In addition, we believe that there will be good acceptance of patients for the internet-based intervention and that internet-based intervention will be more cost effective than the online booklet.

**Trial registration:**

The study was prospectively registered at ClinicalTrials.gov (NCT04274439, registered 18 February 2020).

## Background

Chronic pain is a major burden on the individual and society [1]. It is estimated that about one third of the adult population worldwide suffer from chronic pain, with higher prevalence rates reported for low-income countries [2–5]. In Brazil, the prevalence of chronic pain is around 39% [6] in the adult population, and up to 61% in adult workers [7]. Chronic pain has also been reported as the main reason for people seeking care in outpatient clinics in Brazil [6].

The most common conditions responsible for chronic pain are musculoskeletal disorders of the back, neck and upper limbs; as well as knee and hip osteoarthritis. In the most recent Global Burden of Disease Study, musculoskeletal pain accounted for more than 20% of years lived with disability in the population, and low back pain alone was the leading cause of years lived with disability across the globe [8]. Musculoskeletal pain is responsible for the highest overall healthcare costs of all chronic pain conditions, with most of the costs related to the use of outpatient services [9].

Treatment for chronic musculoskeletal pain is a challenge for clinicians since it is often accompanied by many factors that are associated with pain, such as disability, emotional distress, work absenteeism, reduced quality of life, and even early mortality [10–14]. Therefore, it has been suggested that a multimodal treatment approach focusing on pain management that incorporates both physical and psychosocial factors may address better symptoms of patients with chronic musculoskeletal pain [15–18].

Internet-based self-management programs have grown with the development of new technologies and have been extensively used for delivering healthcare in many areas [19–22]. Internet-based self-management programs overcomes some of the potential barriers that patients face with traditional face-to-face healthcare, such as travel (distance, traffic, transport, and time consumed), high demand of the public health system (e.g. long waiting lists), lack of time, lack of insurance coverage for private care, and high costs for long-term treatment. Previous studies have shown that internet-based self-management programs may be effective for reducing pain and disability in patients with chronic pain [23, 24]. However, there is still little research on the development and testing of remotely-delivered programs for the management of chronic musculoskeletal pain, especially in low- and middle-income countries.

The aim of this clinical trial is to develop and test the effectiveness and cost-effectiveness of an internet-based self-management program based on pain education and exercise for people with chronic musculoskeletal pain.

## Methods

### Elaboration protocol

This study protocol follows the recommendations of the SPIRIT Statement [25] for clinical trial protocols elaboration and is reported according to the CONSORT Statement [26].

### Study design

This is a prospectively registered, assessor-blinded, two-arm randomised controlled trial with economic evaluation.

### Settings and eligibility criteria

Patients will be recruited from the community in Brazil. We will include patients aged between 18 and 60 years, seeking treatment for any chronic musculoskeletal pain condition. Eligibility criteria are: pain of at least 3 points on a 0 to 10 Pain Numerical Rating Scale, able to read and understand Portuguese and with internet access. Chronic pain will be defined as pain lasting more than 12 weeks [27].

Exclusion criteria are: nerve root compromise, serious pathologies (e.g., fracture, tumor, inflammatory, autoimmune, and infectious diseases), serious cardiovascular and metabolic diseases (e.g., coronary heart disease, cardiac insufficiency, decompensated diabetes), recent orthopaedic surgery (over the last 12 months), scheduled to undergo surgery in the next six months, or pregnancy. Patients will also be excluded if there is any contraindication to exercise. We will pre-screen for physical activity participation at baseline using the Physical Activity Readiness Questionnaire (PAR-Q) Portuguese version [28, 29].

### Procedure

The blinded assessor will screen potential participants to determine eligibility. Eligible patients will receive the online consent form and will be informed about the aims of the study. The blinded assessor will then collect the patient’s sociodemographic data, medical history, and the data related to the study outcomes for baseline assessment. The baseline assessment will be performed via videoconference using a personalised link using Whereby platform. All other assessments will be collected by telephone calls, smartphone messages or e-mail (8 weeks, 6, and 12 months after randomisation) through a questionnaire created on the Typeform platform (Fig. 1). All data entry will be coded and double-entered into a Microsoft Excel spreadsheet. A second blinded researcher will double-check the data prior to the analysis.

**Fig. 1 Fig1:**
[figure not shown]
SPIRIT recommended content for schedule of enrolment, interventions, and assessments

### Outcome measures

The primary outcome will be pain intensity at 8 weeks measured using the Pain Numerical Rating Scale [30], a numerical scale where 0 indicates no pain and 10 indicates maximum pain intensity.

The secondary outcomes will be as follows:
Pain intensity at 6 and 12 months follow-ups;Function at all time points, measured with the Patient Specific Functional Scale [30], a self-reported scale specific for the measurement of functionality, where the patient nominates activities relevant to them and rates their ability to perform each activity on a 0 to 10 scale, with 0 representing “unable to perform activity” and 10 represents “able to perform at the same level as before injury or problem”;Health-related quality of life at all time points, measured with the SF-12 [31], a self-reported questionnaire with 12 questions and classification of 8 different dimensions related to quality of life. Higher scores reflect better quality of life;Kinesiophobia at all time points, measured with the Tampa Scale of Kinesiophobia [32], a self-reported questionnaire with 17 items scored on a four point likert agreement scale (“totally disagree” “partially disagree”, “partially agree”, “totally agree”. Three items [4, 8, 12] are reverse scored. Higher scores on Tampa reflect higher kinesiophobia;Global perceived effect at all time points, measured with the Global Perceived Effect Scale [30], a self-reported scale, with scores of − 5 to + 5, where the progression of the patient’s condition will be classified from a certain point in time. Scores of − 5 indicate the condition is vastly worse while scores of + 5 indicates completely recovered.Anxiety and depression at all time points, measured by the Hospital Anxiety and Depression Scale [33], a self-reported scale with 14 items, 7 for depression and 7 for anxiety. Each item is scored on 0 to 3 scale. Higher scores indicate higher depression or anxiety.Pain catastrophisation at all time points, measured with the Pain Catastrophising Scale [34], a self-reported scale with 13 statements, where the patient ranks the affirmations between 0 being “minimal” to 4 “very intense.” The calculation of the final score is based on 3 subdomains of the scale and higher scores represent higher catastrophising.Pain-related attitudes and beliefs at all time points, measured with the Short Form Orebro Musculoskeletal Pain Questionnaire [35], with 10 items related to musculoskeletal pain each scored from 0 to 10 with total score ranging from 0 to 100. Patients with scores between 51 and 100 points are classified as high risk of developing long-term disability.Self-efficacy at all time points, measured with Pain Self-Efficacy Questionnaire [36], a questionnaire with 22 questions classified in three domains, with a score of each domain ranging from 10 to 100. A total score close to 300 indicates a greater sense of self-efficacy.Adverse events measured by recording the number of adverse events during the intervention period.

We will also assess the patient’s expectancy for improvement at baseline using the Expectancy of Improvement Numerical Scale [37].

The same outcome measures will be used at the baseline assessment, post-intervention (8 weeks), 6 and 12 months after randomisation.

Eligible participants will be randomly allocated to one of the treatment groups through an electronic platform. After baseline screening, patients will receive a login and password to access the study website. When the patient logs on to the website, he/she will be randomly allocated to one of the two study groups. The assessor who will confirm the eligibility will be unaware about patients’ allocation.

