The total duration of the intervention will be 8 weeks. There will be new content each week of the intervention and patients will be instructed to perform the exercises from the video at least three times per week and watch the videos as much as needed. Patients in this group will also receive weekly text messages and health coaching over the telephone. The text messages will include information on the benefits of exercises, motivation, and positive messages about dealing with pain. The health coaching will be performed once a week until the end of the intervention (8 weeks) by a physiotherapist (5 years of experience) with previous training for the coaching. The aim of the health coaching component is to keep patients motivated to engage with the program. This will include encouragement, motivation, coping, review of the instructions, and if necessary, tailoring of the content of the intervention. For example, if a patient feels any discomfort while doing an exercise, the coach will slightly modify the exercise (e.g. dose, range of motion). Adherence to the program will be recorded in a daily log.

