We will perform cost-effectiveness and cost-utility analyses according to the intention-to-treat principles [41]. Differences in costs and effects will be estimated using seemingly unrelated regression analyses. The incremental cost-effectiveness ratios will be calculated by the difference between intervention costs divided by the difference between intervention effects. Bootstrapping techniques will be performed to estimate uncertainty surrounding the cost difference and incremental cost-effectiveness ratios. The cost-effectiveness analysis will be conduct for pain intensity at 12 months after randomisation. The cost-utility analysis will be conducted using the health utility index measured by the SF-6D (derived from the SF-12) to calculate the quality-adjusted life-years (QALY). Two exploratory sensitivity analysis will be performed, one including the total costs of the intervention (including costs with preparing and developing the website and videos) diluted in a 10-year period, considered as the available period of use of the resource. The second sensitivity analysis will be performed considering only patients with more than 75% of adherence to the program.

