#### Data analysis

The normality of the data will be tested by visual inspection of histograms. Baseline characteristics of the participants will be calculated using descriptive statistics. The between-group differences and 95% confidence interval for the post-treatment outcomes at 8 weeks, 6- and 12-months follow-ups will be calculated using Mixed Linear Models using interaction terms of treatment group versus time. An intention-to-treat approach will be used in all statistical analyses.

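### Adverse events are counted only during the 8-week intervention, so the 12-month benefit and cost-effectiveness results will have no matching adverse-event record

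*Protocol article*

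**What the plan says.** All references are to the protocol article.

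- *Outcome measures*, last secondary outcome: "Adverse events measured by recording the number of adverse events during the intervention period".
- *Internet-based pain education and exercise* gives the length of that period: "The total duration of the intervention will be 8 weeks".
- *Outcome measures*, primary outcome: "The primary outcome will be pain intensity at 8 weeks measured using the Pain Numerical Rating Scale". Pain later on is secondary: "Pain intensity at 6 and 12 months follow-ups". The remaining patient-reported secondary outcomes are each listed for every assessment. Adverse events are the only secondary outcome whose collection is confined to the treatment period.
- *Outcome measures*, closing part: "The same outcome measures will be used at the baseline assessment, post-intervention (8 weeks), 6 and 12 months after randomisation".
- Abstract, *Methods*: "Follow-ups will be conducted in post-treatment, 6 and 12 months after randomisation".
- *Data analysis* plans "between-group differences and 95% confidence interval for the post-treatment outcomes at 8 weeks, 6- and 12-months follow-ups".
- *Economic evaluation* takes a 12-month horizon and bases the cost-effectiveness analysis on pain at 12 months.

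**The concern.** The trial will estimate effects at 6 and 12 months and cost-effectiveness at 12 months, and the *Discussion* looks ahead to use in health services. A reader of those results will want to know what harm occurred over the same time. As the plan stands, the adverse-event count ends at week 8.

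This is a stated collection window, not a detail left to an analysis plan. Events that were not collected cannot be recovered at the analysis stage.

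The gap matters more if patients go on exercising after week 8. Weekly coaching ends then, and the coach is the only person the article names as adapting an exercise that causes discomfort. The article does not say whether patients continue. That they do is an assumption, though a reasonable one for a programme that aims at self-management.

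**Working it through.** The plan gives no figure for adverse events. Its one design calculation, the sample size for pain at 8 weeks, is neither used nor changed by this point.

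**Step 1. Share of follow-up without an adverse-event record.** Inputs: intervention of 8 weeks (*Internet-based pain education and exercise*) and last follow-up at 12 months, taken as 52 weeks (abstract, *Methods*).

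- Covered: 8 / 52 = 15.4%.
- Not covered: (52 − 8) / 52 = 44 / 52 = 84.6%, about 85%.
- In days the result is the same: 1 − 56 / 365.25 = 84.7%.

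This is a share of calendar time. It is not a share of risk or of exposure to the exercises.

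**Step 2. Which conclusions the window matches.**

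| Conclusion | Time point | Inside the adverse-event window? |
|---|---|---|
| Pain, primary | 8 weeks | Yes |
| Pain and other secondary outcomes | 6 and 12 months | No |
| Cost-effectiveness | 12 months | No |

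**Step 3. What is still collected after week 8.** Global Perceived Effect runs from −5 (vastly worse) to +5. Pain, function, anxiety and depression are scored at 6 and 12 months. Health-care use, including hospital stays and emergency visits, is costed within the 12-month economic evaluation. Two limits apply. The scales register change in the patient's condition and do not identify events. The health-care costs are those due to chronic pain, so a fall, a new injury or a cardiac event need not appear, and these data are planned as costs rather than as a harm outcome.

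**Step 4. What a late record could show, as an illustration.** Suppose that no late event were seen among n patients in an arm. The exact one-sided 95% upper bound on the risk is 1 − 0.05^(1/n).

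- n = 80 (no loss): 1 − 0.05^(1/80) = 3.7%.
- n = 80 × 0.85 = 68 (15% loss): 1 − 0.05^(1/68) = 4.3%.

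The article does not tie its 15% loss to a time point; applying it at month 12 is my assumption. Without a late record, neither bound can be stated.

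**Step 5. The two statements on timing.** The adverse-event item sets a specific window. The schedule sentence is general and covers all outcome measures. It cannot be taken literally for adverse events, because a count made during the intervention cannot be made at baseline. The specific clause is the natural one to follow, but the general one leaves room for doubt.

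A related ambiguity is that the 8-week duration is given under the internet programme, whereas the booklet arm's weekly texts run for the study period. The end of the control arm's intervention period is therefore not plainly fixed.

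**The case against.** The strongest case on the other side is that counting adverse events over the treatment period is a recognised design choice and matches the primary endpoint at 8 weeks. The hypotheses concern pain, biopsychosocial outcomes, acceptance and cost-effectiveness, and no 12-month safety conclusion is promised. This stands, and it is why the point is a limitation of the later results and not an error in the main comparison.

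Four stronger readings are tempting, and the document does not support them.

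- *The window contradicts the assessment schedule.* A specific clause stands beside a general sentence, and the planned comparisons in *Data analysis* set no collection window. This is loose wording. The schedule figure (Fig. 1) is not shown and may resolve it.
- *There are no harm data at all after week 8.* Perceived worsening, symptom scores and pain-related care continue to 12 months. What is absent is an adverse-event record.
- *Events in the last week of new content are lost.* Week 8 belongs to the intervention and so lies inside the window. Only events that start or are first recognised afterwards are missed.
- *The 10-year period shows that patients go on using the programme.* The words "diluted in a 10-year period, considered as the available period of use of the resource" concern the spreading of website and video development costs in a sensitivity analysis. They describe the life of the resource, not the exposure of a patient.

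It is also fair to say that the bounds in the working are hypothetical and show no bias or loss of power. They indicate only what a late record could offer.

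**Conclusion.** The point holds as a minor one. Under the stated window no adverse-event record is planned for 44 of 52 weeks (85%), although benefit is estimated at 6 and 12 months and cost-effectiveness at 12 months. The primary comparison is not affected, and neither are the sample size and power.

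The conclusion rests on reading the intervention period as 8 weeks in both arms and on Fig. 1 not showing a longer adverse-event schedule. It does not depend on patients continuing to exercise after week 8, though the practical importance of the gap does.

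**What to change.** 1. In *Outcome measures*, define the adverse-event window as randomisation to 12 months for both arms. A calendar window also removes the doubt about where the control arm's intervention period ends.
2. Put the same closed item in the Typeform questionnaires at 8 weeks, 6 and 12 months in both arms: for example, any new injury, marked worsening or new symptom that led to seeking care, and whether it led to an emergency visit or admission.
3. Report the number of patients with at least one event, by arm, separately for weeks 0 to 8 (the main harm comparison) and week 8 to month 12.
4. Reword the general schedule sentence to agree with the adverse-event item, and check both against Fig. 1.

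The cost is one or two items in questionnaires that are already sent. The drawback is recall: about 26 − 8 = 18 weeks at the 6-month questionnaire and 52 − 26 = 26 weeks at the 12-month one. That is why the 0 to 8 week comparison should stay the main one. If the window is kept as it is, the 12-month reports should say that no adverse-event record exists after week 8.

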### Blinding

The outcome assessor will be blinded to the treatment groups. The assessor will be asked to guess which group the patients were in (intervention or control) at the end of the study to measure assessor blinding. Due to the nature of the interventions, it will be not possible to blind neither the patients nor treatment providers.

### Interventions

#### Internet-based pain education and exercise

Patients allocated to the intervention group will receive a login and password for individual access to the website designed for the study (www.reabilitador.com.br). The content of this intervention will include videos and animations based on pain education, physical activity promotion and general exercises. The pain education component will be based on the E-pain intervention developed by Reis at al [38], .which includes nine main features: (1) acceptance, (2 and 3) pain education, (4) sleep hygiene, (5) recognising stress and negative emotions, (6) increasing positive coping in lifestyle, (7) exercises, (8) communication and (9) prevention. The exercise program was created by professional physiotherapists with at least 5 years of clinical experience, specialists in the treatment of chronic pain and who used exercise-based treatment. After its elaboration, it was submitted to a round of suggestions and adjustments to the program by a panel of experts. After this round of suggestions, the exercise component was sent by email to a group of experts in the chronic pain field. After the last round of suggestions and corrections, the exercise program was modified to be simple and assertive for the Brazilian population. The exercise component includes general exercises aiming to improve strength, flexibility, control and coordination.

The total duration of the intervention will be 8 weeks. There will be new content each week of the intervention and patients will be instructed to perform the exercises from the video at least three times per week and watch the videos as much as needed. Patients in this group will also receive weekly text messages and health coaching over the telephone. The text messages will include information on the benefits of exercises, motivation, and positive messages about dealing with pain. The health coaching will be performed once a week until the end of the intervention (8 weeks) by a physiotherapist (5 years of experience) with previous training for the coaching. The aim of the health coaching component is to keep patients motivated to engage with the program. This will include encouragement, motivation, coping, review of the instructions, and if necessary, tailoring of the content of the intervention. For example, if a patient feels any discomfort while doing an exercise, the coach will slightly modify the exercise (e.g. dose, range of motion). Adherence to the program will be recorded in a daily log.

